### Recruitment {15}

Recruitment will be performed by anaesthesia staff of the participating clinics during usual preoperative visits.

### Assignment of interventions: allocation

#### Sequence generation {16a}

Randomisation is performed as block randomisation with permuted blocks of variable length by staff members of the coordinating study centre. Random numbers are obtained from www.random.org. Each individual set of randomisation envelopes contains 50% of each group for equal distribution of the groups per centre. An Excel® Spreadsheet was created with 45 sets of 100 randomisations each. For each set, a random number of blocks with a random and even-numbered length were created.

#### Concealment mechanism {16b}

Opaque envelopes are sent to the participating clinics. These contain the case report form and the group allocation. Measures are adopted to prevent access from unauthorised persons.

#### Implementation {16c}

The allocation sequence with random IDs in ascending order is generated by staff members of the coordinating study centre and assigned to the opaque randomisation envelopes. Patients are enrolled by the study staff in the participating clinics during the preoperative visit and assigned by using the randomisation envelopes in ascending order.

### Assignment of interventions: blinding

#### Who will be blinded {17a}

This study is designed patient- and observer-blinded. The intervention is applied only during the maintenance of general anaesthesia. Thus, the patient remains blinded to the intervention. All patients receive opaque dressings on the intervention sites on both forearms. The patient’s group assignment and intervention remain hidden from the PACU nurses as they gather the primary endpoint as well as the staff that collects data during the follow-up. Data analysis will be performed blinded as well.

#### Procedure for unblinding if needed {17b}

Unblinding of the intervention is permitted after contacting the coordinating study centre if (serious) adverse events occur.

### Data collection and management

#### Plans for assessment and collection of outcomes {18a}

Baseline data (gender, age, risk factors for PONV, etc.) is recorded during the preoperative visit. Additional information is recorded during the anaesthetic procedure including the administered medication. Outcomes and medication are assessed during the stay in the postanaesthesia care unit and on the first postoperative day in the ward by the anaesthesia staff of the participating clinics. These include the following tools.

The Postoperative Nausea and Vomiting Intensity Scale (PIS) provides a clinical evaluation of nausea, retching, and vomiting and allows for differentiation between transient and mild nausea symptoms and clinically relevant PONV (see Additional file 2) [24]. The nursing staff fills in the PIS in the PACU and patients themselves complete the PIS on the first postoperative day.

PPP33 is a questionnaire measuring the perioperative quality of life (see Additional file 3). It contains 33 questions. Answers to individual questions are valued from 1 to 4. An overall score—containing eight sub-scales representing eight different dimensions (information, fear, autonomy, pain, physical complaints, rest, communication, accommodation) of the perioperative quality of life—can be calculated. Higher scores indicate a higher quality of life [26, 27].

PON-F is used for the assessment of side effects of antiemetic drug combinations (see Additional file 4). PON-F consists of 38 items representing symptom descriptions organised by body regions. The symptoms and the physical constraints caused by these symptoms can be rated as ‘severe’, ‘moderate’, ‘mild’, and ‘not present’. Additionally, the patient must decide whether the symptom is related to anaesthesia. The objective is to ascertain the antiemetic-related side effects with a focus on their incidence and the simultaneous administration of various antiemetics.

#### Plans to promote participant retention and complete follow-up {18b}

The study staff assesses the outcomes until the first postoperative day. Administered antiemetic medication is documented as it can be obtained from the patient record.

#### Data management {19}

Data collection is facilitated using a paper-based case report form (CRF) and fed into a web-based database by the investigators. Additionally, the data collection includes baseline data gathered during the admission interview, the anaesthesiologist’s intended antiemetic prophylaxis, and data on anaesthesia management, the course in the recovery room, and the need for antiemetic rescue medication in the first 24 h. The CRF is supplemented by patient-related outcomes form consisting of a three-page questionnaire containing PIS, PPP33, and PON-F filled out by the patients on the first postoperative day.

##### Database infrastructure

The web-based database was created using typical web standards and is hosted by the university computer centre of Philipps-University of Marburg. Access is restricted to study staff by login. Input formats are validated, and an audit trail was established to ensure data integrity. Coding of data is performed after the submission of the data form. The corresponding coding can be found on the paper-based CRF. Regular backups of the database are performed.

#### Confidentiality {27}

Pseudonymisation is ensured by using the corresponding ID in the database. The ID is linked to the clinic’s patient ID by lists which are maintained in the study centres.

#### Plans for collection, laboratory evaluation, and storage of biological specimens for genetic or molecular analysis in this trial/future use {33}

n/a: No biomaterial obtained

## Statistical methods

### Statistical methods for primary and secondary outcomes {20a}

Statistical evaluation is performed using RStudio version 1.2 (RStudio Team (2018): Integrated Development for R. RStudio, Inc., Boston, MA. URL http://www.rstudio.com/). Statistical significance is generally assumed at a *p*-value < 0.05.

To check for homogeneity between the two groups, the Pearson *χ*^2^-test is used for nominal scale levels. Student’s *t*-test for independent samples is used for continuous data after performing the Shapiro-Wilk test and the Levene test. The non-parametric equivalent is the Mann-Whitney *U* test.

Metric data are reported as the arithmetic mean, standard deviation, or median with 25% and 75% quantile. Ordinal data is given as median with 25% and 75% quantiles.

Scores of the tools used for assessing the outcome are calculated as intended by tools’ authors.

### Interim analyses {21b}

We plan to perform an interims analysis after recruitment of 50% of patients (*n* = 1750 patients). It is intended to use the secondary endpoint ‘severity of PONV’ since this is a suitable indicator for the primary endpoint ‘incidence of PONV’. A threshold of a *p*-value ≥ 0.1 is defined as an indicator of futility and will cause the termination of the study. If the *p*-value is below this threshold, the study will be completed as planned.

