### Outcomes {12}

#### Primary endpoint

The primary outcome measure for this study is the incidence of PONV within a 24-h observation period. PONV is defined as nausea, retching, vomiting, or the need for any antiemetic medication during the observation period.

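### The mandatory futility stop is tested on PONV severity as a stand-in for incidence, although 24-h incidence, the outcome the trial is sized on, is observed by the same visit in the same 1750 patients

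*Protocol article*

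**What the plan says.** All references are to the protocol article.

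- **Interim analyses {21b}:** the look is taken at half of recruitment ("We plan to perform an interims analysis after recruitment of 50% of patients", 1750 in total). The outcome is severity, and the reason given is: "It is intended to use the secondary endpoint ‘severity of PONV’ since this is a suitable indicator for the primary endpoint ‘incidence of PONV". The consequence is binding: a p-value "≥ 0.1 is defined as an indicator of futility and will cause the termination of the study".
- **Primary endpoint, under Outcomes {12}:** "The primary outcome measure for this study is the incidence of PONV within a 24-h observation period", and "PONV is defined as nausea, retching, vomiting, or the need for any antiemetic medication during the observation period".
- **Secondary endpoints:** intensity of PONV over the same 24 h, classified with the PIS.
- **Plans for assessment and collection of outcomes {18a}:** the PIS "provides a clinical evaluation of nausea, retching, and vomiting and allows for differentiation between transient and mild nausea symptoms and clinically relevant PONV". On timing, "The nursing staff fills in the PIS in the PACU and patients themselves complete the PIS on the first postoperative day".
- **Ward (first postoperative day)** puts that visit at 22–26 h after the end of anaesthesia. **Data management {19}** says that rescue antiemetic need in the first 24 h is also collected.
- **Sample size {14}** rests on incidence, 25% against 20%.
- **Abstract, Methods** differs from all of this: it makes incidence and severity together the primary endpoint, and then lists severity again as secondary.

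**The concern.** The outcome that decides whether the trial goes on is not the outcome that decides its conclusion. A substitute at an interim look is normally justified by being available sooner. Here it gains no time, and {21b} offers no data for the claim that severity stands in well for incidence.

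The two outcomes weight patients differently. Someone with brief mild nausea is a full primary event but would presumably rank low on a graded scale. Someone counted only through antiemetic need is a full primary event, yet the description of the PIS in {18a} mentions no such component.

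Two errors follow. A trial that delivers the planned fall in incidence can be stopped because severity did not separate enough. A trial with no effect on incidence can be kept running because severity shifted.

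**Working it through.** **The plan's own figures.** Half of 2 × 1750 = 3500 is 1750, so the interim size reproduces: 875 per arm at 1:1. The protocol gives no operating characteristics for the interim rule. The sample size of 1503, read as per arm, does not reproduce at the stated 80% power: 25% vs 20% at two-sided 5% needs 1094 per arm (1134 with continuity correction), and 1503 gives about 91%. That is a separate matter and does not enter below.

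**Inputs.** 25% vs 20% from {14}; 875 per arm and the 0.1 threshold from {21b}; 1750 per arm at the end. {21b} names no test, so a two-sided test is assumed.

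**Availability.** Both outcomes cover 24 h. The PIS is filled in in the PACU and on day 1, the visit is at 22–26 h, and rescue antiemetic use is on the CRF. Incidence is therefore observed no later than severity.

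**Step 1: interim on incidence.** P(continue) = Φ((δ − 1.645·s0)/s1), with pooled s0 and unpooled s1.

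- s0 = √(2 × 0.225 × 0.775 / 875) = 0.01996
- s1 = √((0.25 × 0.75 + 0.20 × 0.80) / 875) = 0.01993
- (0.05 − 1.645 × 0.01996) / 0.01993 = 0.861, and Φ(0.861) = 0.805

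The stop probability is 1 − 0.805 = 19.5% (about 21% with Fisher's exact test).

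**Step 2: overall power with incidence at the interim.** With no interim and 1750 per arm, s0 = 0.01412 and s1 = 0.01409, so (0.05 − 1.96 × 0.01412) / 0.01409 = 1.585 and power is about 94%. Simulating both stages, with success meaning p < 0.1 at the interim and p < 0.05 at the end, gives about 79%.

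**Step 3: interim on severity, same threshold.** PIS scoring is in an additional file that is not shown, so each reading below is an assumption. The ordinal rows are simulated with a Mann-Whitney test. Except in the second row, scores run from 1 to 10, uniform in sufferers unless shifted. The yes/no row applies the Step 1 formula to rates 0.25f and 0.20f. At f = 0.5, for example, 12.5% vs 10% gives (0.025 − 1.645 × 0.01511) / 0.01509 = 0.01, a stop of about 50%.

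| Interim outcome | Stop probability at true 25% vs 20% |
|---|---|
| Incidence (primary) | 19.5% |
| Ordinal score, every primary event above zero, severity in sufferers unchanged | about 21% |
| Three-level ordinal score, benefit on mild events only, clinically relevant events equal in both arms | about 26% |
| Ordinal score, 10 / 20 / 30% of primary events scoring zero | about 25 / 31 / 36% |
| Ordinal score, all events above zero, severity in sufferers also 10% / 20% lower | about 13% / 9% |
| Yes/no clinically relevant PONV, share f = 80 / 67 / 50 / 33% of primary events | about 30 / 38 / 49 / 63% |

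Repeat runs differ by about one percentage point. For the yes/no row, overall power is about 69 / 61 / 50 / 37%.

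**Step 4: the reverse error.** If P6 leaves incidence unchanged, the test on incidence stops about 90% of the time by construction. If P6 nevertheless makes episodes milder, the test on severity stops less often, and the trial continues although it is futile on its primary endpoint.

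**The case against.** The strongest case against is that the cost may be negligible or even negative.

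- **Scoring.** The large stop rates need severity collapsed to a yes/no variable. The protocol says only that the PIS "allows for differentiation between transient and mild nausea symptoms and clinically relevant PONV". {20a} says that scores follow the tools' authors and names the Mann-Whitney test as its non-parametric option. On a graded score that keeps every event, the loss against incidence is a point or two.
- **Direction.** If P6 also softens the remaining episodes, a graded score is the more sensitive test.
- **Overlap.** The PIS covers the same three symptoms as the primary. The only documented gap in coverage is patients counted solely through antiemetic need, and nothing says how many there are.
- **Abstract.** It places severity within the primary endpoint.
- **Missing data.** {18b} takes antiemetic use from the patient record as far as it can be obtained, and {20c} expects missing values. Incidence is therefore observed by the same visit, but not necessarily complete.

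All of this stands as a limit on size and direction. It does not supply a reason for the substitution. The abstract does not rescue it either: {21b} itself calls severity secondary and incidence primary, in agreement with Outcomes {12}.

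**Conclusion.** The point holds as an unjustified choice of interim outcome. The stop is mandatory, the substitute gains no time, and the trial is sized on incidence. The interim test can disagree with the primary in either direction.

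The size is uncertain. Against 19.5% on incidence, the stop probability under the planned effect is about 21% on an ordinal score that keeps all events and about 25–36% if 10–30% of primary events score zero. It is lower than on incidence if episodes also become milder. The zero-score shares and severity shifts are assumptions.

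A reader might infer that the endpoint choice costs over 40 points of stopping probability (63% against 19.5%), or that severity always misses a true effect more often. The documents support neither. The first needs a yes/no severity outcome, and a share of events, that appear nowhere in the protocol. The second fails once severity in sufferers also falls.

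Much of the power loss belongs to the threshold, not to the endpoint: p ≥ 0.1 alone takes power from about 94% to about 79%, even on incidence. This is a cheap improvement worth making, not a fatal flaw.

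**What to change.** In Interim analyses {21b}, replace severity with the primary endpoint, for example: *At the interim, 24-h incidence of PONV as defined under Primary endpoint {12} is compared between groups with the test planned for the final primary analysis; PIS intensity is summarised descriptively only.* Delete the sentence that offers severity as a proxy. Reconcile the Abstract, which makes incidence and severity the primary endpoint, with Outcomes {12} and {21b}.

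**Cost.** About one sentence, with no new data, visits or patients. The downside is one unblinded look at the primary before the end, and the loss of any sensitivity that a graded score might add. Because the rule can only stop for futility, the look does not inflate the type I error. The change does not repair the power lost to the 0.1 threshold, which needs its own decision.

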### Sample size {14}

Sample size calculation assumes a baseline incidence of PONV of 25%. This number is lower than reported in surveys on PONV with 29% [25] but considers routine pharmacological prophylaxis, at least in patients with increased risk for PONV.

A Cochrane review by Anna Lee [17] suggests that P6 stimulation can reduce PONV by approximately 30% (relative risk reduction), leading to a PONV-incidence in the treatment group of 17.5%. The trial is powered to detect an absolute reduction of 5% points (from 25 to 20%). This conservative estimation of P6 treatment considers that efficacy will not be as perfect as in efficacy trials, e.g. due to inconsequent or erroneous administration of the P6 stimulation. Power analysis was performed with PASS 2002 (Number cruncher software) and revealed that 1503 patients provide a power of 80% to detect an absolute 5% point difference with a type I error of 5% using the two-sided Fisher’s exact test. With an added safety margin of about 15% compensating for dropouts, etc. 2 × 1750 patients must be included.

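### The mandatory futility stop at p ≥ 0.1 on PONV severity would end about one in four trials with the planned effect and take overall power below the stated 80%

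*Protocol article*

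**What the plan says.** Interim analyses {21b} sets one look when half the patients (1750) have been recruited. It uses PONV severity in place of incidence, "since this is a suitable indicator for the primary endpoint". A p-value of 0.1 or more "is defined as an indicator of futility and will cause the termination of the study"; below that value the trial runs to its planned end. The section names no test, sidedness or direction of effect. Dissemination plans {31a} also foresees early termination under these criteria.

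Outcomes {12} defines the primary endpoint as 24-hour PONV incidence and lists intensity, measured with the PIS, as secondary.

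Sample size {14} plans for 25% versus 20% and says that "1503 patients provide a power of 80% to detect an absolute 5% point difference". The test there is Fisher's exact test, two-sided at the 5% level. For losses the section adds: "With an added safety margin of about 15% compensating for dropouts, etc. 2 × 1750 patients must be included". It does not mention the interim look.

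**The concern.** A futility rule should stop a trial that has little chance of succeeding. This one asks for something close to a positive result on half the data and otherwise ends the trial. Every trial with a real effect that happens to fall short at half-way is lost, so the power in {14} is not the power of the design as it will be run.

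There are two further problems. The decision rests on a variable other than the primary one, and the two can disagree. And because no direction is given, a result with p < 0.1 in favour of control leads, as written, to completion of the study.

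A trial stopped by this rule would leave the primary question unanswered at a size that was never meant to answer it.

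**Working it through.** **Inputs.** From {14}: incidence 25% and 20% (difference 0.05), two-sided 5% final test, 1503 evaluable per arm, 1750 recruited per arm. From {21b}: look at half recruitment, stop if p ≥ 0.1. Assumed, because the document does not say: the interim p is two-sided (critical value 1.645), and the severity test carries the same standardised signal as the incidence test. Both are varied below.

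**The plan's own figure.** For 25% versus 20%, 80% power needs 1094 per arm (1134 with continuity correction; exact Fisher power there is 80.1%). At 1503 per arm, power is 90.7% by the normal approximation and 90.0% by exact Fisher calculation. The continuity-corrected formula for 90% power gives 1504. So 1503 per arm is a 90%-power size labelled 80%. This is a separate slip, but it explains why the baseline below is 90% and not 80%.

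**Effect of the rule.** Let SE₀(n) = √(2·0.225·0.775/n) be the null standard error and SE₁(n) = √((0.25·0.75 + 0.20·0.80)/n) the standard error under the planned effect. Then

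- a = (0.05 − 1.645·SE₀(n₁))/SE₁(n₁), and P(stop) = 1 − Φ(a);
- b = (0.05 − 1.96·SE₀(n₂))/SE₁(n₂), and power without the rule = Φ(b);
- power with the rule = Φ₂(a, b; ρ), with ρ = √(n₁/n₂) = 0.707.

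At 752 and 1503 per arm:

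- a = (0.05 − 1.645·0.02154)/0.02150 = 0.677, so P(stop) = 24.9%.
- b = (0.05 − 1.96·0.01523)/0.01521 = 1.325, so power without the rule is 90.7%.
- Power with the rule is 73%.

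At 875 and 1750 per arm (no losses), a = 0.861 and b = 1.585. This gives 19.5% stopping, and power falls from 94.3% to 79.2%.

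Simulation (400,000 trials per setting) agrees. With a continuity correction, which approximates Fisher's test, the figures are:

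| Per arm, interim/final | P(stop) | Power without rule | Power with rule |
|---|---|---|---|
| 751/1503 | 26.8% | 90.0% | 71.0% |
| 875/1750 | 20.8% | 93.9% | 77.8% |

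If the stated 80% is taken at face value (547 and 1094 per arm), the rule stops 36.8% and leaves 59.1%.

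**Is p = 0.1 futile?** At 752 per arm the rule requires an observed difference above 1.645·0.02154 = 3.5 points, when 5 are planned. Conditional power at z₁ = 1.645 and t = 0.5 is 1 − Φ((1.96 − z₁√t − θ(1 − t))/√(1 − t)).

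- Planned effect, θ = 0.05/0.01521 = 3.29: (1.96 − 1.163 − 1.644)/0.707 = −1.20, giving 88%.
- Observed trend, θ = 1.645/0.707 = 2.33: (1.96 − 1.163 − 1.163)/0.707 = −0.52, giving 70%.

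**Sensitivity.** The ranges cover 752/1503 and 875/1750 per arm. The rows on severity signal take a correlation factor of 0.8 between the two endpoints.

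| Change of assumption | P(stop) | Power with rule |
|---|---|---|
| Severity signal 10–20% weaker | 27–42% | 57–71% |
| Severity signal 10% stronger | 13–18% | 78–84% |
| Severity signal 20% stronger | 9–13% | 82–88% |
| One-sided interim p | 11–15% | 82–87% |
| True rate 17.5% instead of 20% | 1–3% | 97–98% |
| True effect 4 points | 36–44% | not needed here |

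A simulated rank test on a severity score with zeros for unaffected patients gives 25% and 19% stopping, in line with the base case. If severity were compared only among patients with PONV and P6 did not change it in them, that test would be under its null hypothesis and p ≥ 0.1 would occur about 90% of the time. The document does not say which patients the comparison covers.

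**The case against.** The strongest reply is that the figures depend on what {21b} leaves open. With a one-sided interim p, power stays above 80%. If severity is clearly more sensitive than incidence, it does too. The 15% is called a safety margin and may not be used up; with no losses the shortfall from 80% is only one to two points. At the review-based rate of 17.5% the rule is almost harmless. A sponsor may also knowingly give up power to stop early when there is no effect, and a futility stop does not inflate the type I error. Severity is close to the primary construct, and the abstract even names incidence and severity together as the primary endpoint. Finally, the case-only scenario is a possibility; nothing in the text restricts the PIS to cases.

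Much of this stands as a caveat, and the figures should be quoted with their conditions. It does not remove the point. The only sidedness the document states for a test of the treatment effect is two-sided. Nothing shows severity to be the stronger measure, and a weaker signal makes the loss larger. The protocol chose 20% rather than 17.5% because it expects less than ideal application in routine use, so that is the effect against which its power must be judged. If power was traded for early stopping on purpose, {14} should say so, and it does not.

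**Conclusion.** The concern holds. At 25% versus 20%, with a two-sided interim p and severity as sensitive as incidence, the rule ends 25–27% of trials at the planned evaluable numbers and 19–21% with no losses. Overall power is 71–73% and 78–79% respectively. Both are below the stated 80%, although the sample size without the rule carries 90% or more. The rule therefore uses up the whole unacknowledged surplus and more.

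Power returns above 80% only if the interim test is one-sided, if severity is clearly more sensitive than incidence, or if the true effect is well above the planned one. The document supports none of these as the design assumption. The choice of a secondary endpoint and the missing direction are faults whatever the exact percentages.

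**What to change.** Rewrite {21b} so that the look tests 24-hour PONV incidence in the direction of fewer cases with P6, with a threshold that leaves power nearly intact. Two examples at 752 and 1503 per arm under 25% versus 20%:

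| Stop if interim z is | False stop | Overall power | Stops if no effect | Expected enrolment if no effect |
|---|---|---|---|---|
| ≤ 0 | about 1% | about 90% | about 50% | 3500 − 0.50·1750 = 2625 |
| ≤ 0.5 | 3–4% | about 89% | 69% | 3500 − 0.69·1750 ≈ 2290 |
| Present rule | 25–27% | 71–73% | about 90% | 3500 − 0.90·1750 = 1925 |

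State the chosen rule and the resulting overall power in {14}, and correct the 80% label on 1503 per arm there. The final 5% level needs no adjustment, because the look cannot stop for efficacy.

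The cost is an amendment and no patients beyond 3500. If P6 stimulation has no effect, roughly 370 to 700 more patients are enrolled on average than under the present rule. The change must be made before anyone has seen interim results by arm. The trial status section gives a first patient in September 2018 and an approximate last patient in December 2022, so the look may already have taken place. In that case a change of wording is not enough: the report should say what was tested, what was found, and what power the design had with the rule in force.

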#### Composition of the data monitoring committee, its role, and reporting structure {21a}

n/a: Investigator-initiated trial, no clinical trial under the German Medicines Act (‘AMG’).

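### The interim futility rule states no direction, so on a two-sided reading a result against P6 with p < 0.1 leads to completion

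*Protocol article*

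**What the plan says.** The Interim analyses section {21b} sets one look: "We plan to perform an interims analysis after recruitment of 50% of patients", which it gives as 1750 patients. On the endpoint it says: "It is intended to use the secondary endpoint ‘severity of PONV", on the ground that severity is a suitable indicator for the incidence of PONV. The rule has two branches. A p-value of 0.1 or more "is defined as an indicator of futility and will cause the termination of the study". If instead the p-value "is below this threshold, the study will be completed as planned". The section names no test, no sidedness and no direction of effect.

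The only sidedness in the article is in Sample size {14}, where the power for the primary endpoint is computed "with a type I error of 5% using the two-sided Fisher’s exact test". The statistical methods section {20a} lists tests without sidedness.

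On oversight, the data monitoring committee entry {21a} reads "n/a: Investigator-initiated trial, no clinical trial under the German Medicines Act". Adverse events are reported to the principal investigator {22}. Quarterly meetings deal with recruitment, problems that arise and submitted data {5d, 23}. Unblinding is possible after adverse events {17b}. The dissemination section {31a} mentions early termination only under the interim criteria.

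**The concern.** A futility rule should separate results that leave a realistic chance of showing benefit from results that do not. This rule looks only at the size of the p-value. A two-sided p-value is small when P6 looks better and equally small when P6 looks worse. Followed as written on that reading, the rule stops a neutral trial but completes one whose interim data point against P6.

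At stake are the 1750 patients still to be recruited, about half of them to P6, in a trial that would then have almost no chance of showing benefit. The article fixes both branches of the rule, so this is a rule that gives the wrong decision in one situation and not a detail left to a fuller document.

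**Working it through.** **Inputs from the article.** Total recruitment is 2 × 1750 = 3500 and the interim is at 50%: 0.5 × 3500 = 1750, which reproduces the stated interim number. Allocation is 1:1, so about 875 per group. The planning rates are 25% (control) and 20% (P6). The interim threshold is 0.1 and the general significance level is 0.05.

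**Assumptions.** The interim test is two-sided. PONV incidence stands in for severity, because no distribution of the severity scale is given. The control rate is 25%. The P6 rates of 28% and 30% are hypothetical; 30% is the mirror image of the planned 5-point benefit.

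**Formula.** Normal approximation for two proportions, with n per group, control rate pC, P6 rate pT and p̄ = (pC + pT)/2:

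- SE0 = √(2·p̄·(1 − p̄)/n)
- SE1 = √((pC(1 − pC) + pT(1 − pT))/n)
- critical difference c = z × SE0, with z = 1.645 for p < 0.1 and 1.960 for p < 0.05
- P(continue on a result against P6) = 1 − Φ((c − (pT − pC))/SE1)

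**Trigger.** With both rates at 25%, SE0 = √(2 × 0.25 × 0.75/875) = 0.0207. An observed excess under P6 of about 1.645 × 0.0207 = 0.034, or 3.4 percentage points, gives p = 0.1. For p = 0.05 it is 1.960 × 0.0207 = 0.041, or 4.1 points.

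**Worked case, P6 rate 30%.** SE0 = √(2 × 0.275 × 0.725/875) = 0.02135 and c = 1.645 × 0.02135 = 0.0351. SE1 = √((0.1875 + 0.21)/875) = 0.02131. Then (0.0351 − 0.05)/0.02131 = −0.70, and 1 − Φ(−0.70) = 0.76.

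| True P6 rate (control 25%) | Against P6 with p < 0.1 (trial continues) | Of which p < 0.05 |
|---|---|---|
| 25% | 5% | 2.5% |
| 28% | 41% | 30% |
| 30% | 76% | 65% |

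Both columns are probabilities over all trials. With 752 evaluable per group (half of 1503), the 25% and 30% rows of the p < 0.1 column become 5% and 70%.

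**A single data set.** Take 219/875 (25%) in control and 263/875 (30%) under P6. The two-sided Fisher p is 0.021, below 0.1, so the written instruction is to complete. The one-sided p towards benefit is 0.99, which would stop the trial.

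**Why this is futility.** Let the interim z be −1.645 (p = 0.1 against P6) at half the information. The planned effect over 1750 per group gives an expected final z of 0.05/√(2 × 0.225 × 0.775/1750) = 3.54. The chance of a final z above 1.96 for benefit is 1 − Φ((1.96 + 1.645 × √0.5 − 0.5 × 3.54)/√0.5) = 1 − Φ(1.91) ≈ 3%, even if the planned effect is true. With no true effect it is practically zero.

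**The case against.** The strongest objection is that the two-sided reading is an inference. The article's only statement of sidedness belongs to a power calculation for incidence, while the interim tests severity and names no test. Futility normally means lack of benefit, and with a one-sided p-value towards benefit the problem disappears: at a P6 rate of 30% the probability of continuing is about 0.01%. This stands as a limit on certainty. Nothing in the article supports the one-sided reading, however, and if it was intended the rule still needs a clause saying so.

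A reader might also infer that the protocol requires completion when P6 is shown to be significantly harmful. That goes too far. The trigger is p < 0.1, while the article sets significance at 0.05, so an excess of 3.4 to 4.1 points would trigger completion without being significant by that standard.

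Nor do the documents make worsening likely. Their planning assumption is a benefit, and the post-trial care section reports no documented harm from the materials. The pharmacological prophylaxis section does warn that P6 stimulation and drug prophylaxis might interfere with each other, but the self-commitment completed before the envelope is opened is there to limit this.

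Finally, a reader might infer that there is no oversight at all. There is adverse event reporting, and there are quarterly meetings and a route to unblinding. None carries a stated authority to stop on an unfavourable interim comparison, so the gap in the rule remains.

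**Conclusion.** The point holds in a limited form. The interim rule omits the direction of effect. On a two-sided reading it sends a result against P6 with p < 0.1 to completion, and no other section states a mandate to stop. That logical gap does not depend on any of the rates above.

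Its practical size does. With no true effect, about 5% of trials would continue on a result against P6, which is half of all continuations. Higher figures need a true worsening that the article gives no reason to expect, and all of them use incidence in place of the severity scale. The omission does not bias the primary analysis or inflate its type I error. It is a worthwhile correction, below the level of an essential one.

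**What to change.** Amend the Interim analyses section so that the trial continues only if p < 0.1 and the interim difference in PONV severity favours P6, with every other result falling under the existing futility branch. State that the p-value is two-sided.

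Alternatively, declare the interim test one-sided towards benefit and set the threshold to match. Two-sided p < 0.1 in favour of P6 corresponds to one-sided p < 0.05. Keeping 0.1 as a one-sided threshold would be more lenient: under the planned 25% against 20%, with 875 per group and incidence as proxy, the probability of continuing would be about 89% instead of 81%.

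The cost is small. The change needs no extra patients or data and adds no opportunity to claim efficacy. The one practical demand is that the direction be read without breaking the blinded data analysis promised in the blinding section {17a}. Either someone outside the analysis who knows the group labels reads it, or a prespecified coded label is used.
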